#### Secondary

An independent examiner will perform the following tests.

• The total number of shoulder muscles with MTrPs will be counted and compared to the baseline measurement findings.

• Passive range of motion of the shoulder will be measured by an handheld digital inclinometer (The Saunders group Inc, Chaska, MN). The range of motion of the non-painful shoulder will be used as reference [49,49,50]. Because the normal range of motion differs from one individual to another, we focus on improvement of limited range of motion during the experiment (both experimental group and control group).

◦ For the measurement of passive external rotation, the patient is in a supine position, with the shoulder in 0° of abduction and rotation, the elbow flexed at 90° and the forearm in a neutral position. This position is defined as the position of 0°. The observer then performs external rotation until pain limits the range of motion or the extreme of the range is reached. The inclinometer is placed against the volar side of the forearm. This range of motion is recorded in degrees. The normal range of motion for external rotation is between 70° and 90°.

◦ For the measurement of passive glenohumeral abduction, the patient is seated upright, and the position of 0° is defined as the upper arm is in a neutral position. While palpating the lower angle of the scapula with the thumb, the examiner elevates the upper arm of the patient until the scapula begins to rotate or pain limits further motion. The inclinometer is placed against the lateral side of the upper arm near the elbow. The range of motion is recorded in degrees. The normal range of motion is 90°.

◦ For the measurement of passive elevation (through flexion), the patient is in the supine position with the arm along the side. This position is defined as the position of 0°. The observer than performs elevation until pain limits the range of motion or the extreme of the range is reached. Then the inclinometer is placed against the medial side of the upper arm near the elbow. The range of motion is recorded in degrees. The normal range of motion is between 165° and 180°

◦ For the measurement of internal rotation the patient is in a prone position. The shoulder is 90° abduction, and the forearm is in neutral position. This position is defined as the position of 0°. The observer than performs internal rotation until pain limits the range of motion or the extreme of the range is reached. The sensor is placed against the volar side of the forearm. The normal range of motion is 70°

◦ For the measurement of horizontal adduction the patient is in a supine position. The arm is in 90° abduction. This position is defined as the position of 0°. The observer performs adduction, while the arm stays in the vertical plane, until pain limits the range of motion or the extreme of the range is reached. The normal range of motion is 135°

• Finally the total number of treatment sessions will be counted. This is done by an assistant, who is not involved in the study by using the administration-software of the practice [see Table 1].

**Table 1 T1:** Overview of variables

**Variable**	**T0 Baseline**	**T1 After 6 wk**	**T2 After 12 wk**	**Measured by**
***Age****	X			Interview
***Gender****	X			Interview
***Work***	X			Interview
***Dominant side affected***	X			Interview
***Duration of the complaints****	X			Interview
***DASH ***DLV	X	X	X	Questionnaire
Use of ***medication***	X	X	X	Interview
Use of ***other therapy***	X	X	X	Interview
***Work ***%	X	X	X	Interview
***Improvement ***(percentage of perceived improvement)		X	X	Interview
***Number of involved muscles***	X	X	X	Assessment
***No. of treatment sessions***			X	Assessment
***Health status ***for baseline comparison	X			RAND-36 DLV
***Existence and severity of symptoms of depression***	X			Beck Depression Inventory
***Shoulder Passive ROM***	X	X	X	Goniometry
• flexion	X	X	X	
• abduction	X	X	X	
• external rotation	X	X	X	
• internal rotation	X	X	X	
• cross body adduction	X	X	X	

*Age, gender and duration of the complaints seem to be important prognostic variables [53].

### Sample size

The initial sample size is based on the assumption that the overall score of the primary outcome measure DASH shows a mean improvement of 15 points [SD = 22] [51]. To test the null hypothesis of equality of treatment at α = .05 with 90% power and assuming a uniform dropout rate of 5%, it was calculated that 52 patients in each group would be sufficient.

### Randomization

After inclusion the patients will be randomly assigned to either the intervention group or the "wait and see" group. The randomisation will be performed by an assistant not otherwise involved in the study by generating random numbers using computer software. Stratification or blocking strategies will not be used.

### Informed consent

The patients will be informed about the study prior to the first assessment and will be asked to give written informed consent.

### Blinding

Blinding of the patients or the physical therapists, who are involved in the treatment, is impossible due to the treatment characteristics.

An independent observer will collect baseline data and outcome data. The independent observer is blinded. The successfulness of the blinding procedure will be evaluated by asking the observer to which group she believes the subjects belong.

### Statistical analysis

For comparisons of prognostic variables on baseline we will use the Student's t test for continuous variables with normal distribution and the chi-square test for categorical variables or continuous variables with non-normal distribution[52]. For the overall score of the DASH (primary outcome measure) we will use the unpaired t-test for normally distributed data or Mann-Whitney Rank Sum-test for non-normally distributed data to assess the difference between the two groups after the treatments. Regression analyses will be used to include prognostic factors, such as the baseline scores like age, gender and duration of the complaints, in the analyses. All significance levels will be set at p < 0.05. All data will be analysed primarily according to intention-to-treat principle. We will use Sigmastat 3.11 and Systat 12 for windows (Systat Inc. Richmond, California, USA) for the statistical analyses.

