### Measurements

Before randomization, all participants will be assessed during an individual baseline test session. They will complete a battery of questionnaires and tests, determining data on social, demographic, and physical factors, and baseline values for the outcome measures. In addition, subjects will complete the DASH, RAND-36-dutch language version, and passive range of motion tests of the shoulder (PROM). During the initial assessment, MTrPs will be identified, based on compression-produced pain that is recognized by patients as their own shoulder pain. If no MTrPs are detected, the subjects will be excluded from the study. All measurements will be performed by the same independent observer, who is not employed by the physical therapy practice (This is to create optimal blinding of the observer, who is now not able to recognise the subjects). The observer is trained in identifying MTrPs and has several years of clinical experience in MTrP therapy. The observer participated in a former reliability study of MTrP palpation. The baseline measurements will be at T0, the second measurement (T1) will be 6 weeks after the first assessment session, the third (T2) will be 12 weeks after the first assessment session. All measurements [see box 1] will be performed outside the physical therapy practice to assure that the observer will not recognise any of the study participants when they come to the physical therapy practice for their treatment. After this first assessment, the patients will be randomly assigned to one of two groups: the intervention group or the control group. The patients in the control group will stay on the waiting list and will not receive any treatment. They are allowed to use over-the-counter painkillers during this 12-week period. After 6 weeks and 12 weeks, respectively, they will be examined by the same blinded observer. After 12 weeks they will receive the same physical therapy program as the experimental group [see Figure 1]. The initial trial ends after 12 weeks, but 6 months and 12 months after the start of the experimental intervention shoulder function of the subjects will be re-evaluated with the DASH-Dutch language version.

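### The test named for the primary DASH outcome has no baseline DASH term, the regression that might supply one is neither clear nor ranked, and the effect measure depends on a normality check

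*Protocol article*

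**What the plan says.** All references are to the protocol article.

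- **Primary test (Statistical analysis).** For the overall DASH score "we will use the unpaired t-test for normally distributed data or Mann-Whitney Rank Sum-test for non-normally distributed data", with the purpose "to assess the difference between the two groups after the treatments". No criterion for judging normality is given, and the sentence contains no covariate.
- **Regression (Statistical analysis, next sentence).** "Regression analyses will be used to include prognostic factors, such as the baseline scores like age, gender and duration of the complaints". The section does not say whether this model is primary, secondary or supportive.
- **Baseline DASH (Measurements; Table 1).** The session before randomisation records "baseline values for the outcome measures", and Table 1 lists the DASH at T0, 6 weeks and 12 weeks.
- **Randomisation.** "Stratification or blocking strategies will not be used".
- **Sample size.** The assumption is that "the overall score of the primary outcome measure DASH shows a mean improvement of 15 points [SD = 22] [51"], with 90% power, α of .05 and 5% dropout, from which "it was calculated that 52 patients in each group would be sufficient".

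**The concern.** The most useful covariate for a 12-week DASH score is normally the same patient's baseline score. It is collected here, yet the test named for the primary outcome does not use it. The regression sentence could be meant to include it, since age, gender and duration are not scores, but a reader cannot tell. A reader also cannot tell which result decides the trial: the t-test, the Mann-Whitney test or the regression.

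Three things are at stake:

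- **Precision.** Variance that baseline DASH would explain stays in the error term.
- **Chance imbalance.** Nothing in the allocation method balances baseline DASH, and the named test does not correct for a gap once it has occurred.
- **The effect measure.** The trial is sized on a mean difference in DASH points, and the Primary outcome section gives minimal detectable changes of 10.70 and 12.75 points. If the normality check sends the analysis to the Mann-Whitney test, the primary result is a rank comparison that cannot be set against any of these figures.

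**Working it through.** **Inputs.** From the documents: difference 15, SD 22, α 0.05, power 90%, dropout 5%, 52 per group. Assumed: a two-sided test, and a baseline-to-12-week correlation r of 0.4, 0.5 or 0.7, because the article gives no value. Evaluable patients per arm: 52 × 0.95 = 49.4.

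**1. The plan's own sample size.** Normal approximation: n = 2 × 22² × (1.960 + 1.282)² / 15² = 45.2, so 46; 46/0.95 = 48.4, so 49. Exact t-test: 46.2, so 47; 47/0.95 = 49.5, so 50. Exact t-test with the Mann-Whitney efficiency factor 3/π: 46.19/0.955/0.95 = 50.9, so 51. The stated 52 is reproduced within one or two patients by the last two routes. A one-sided test would need only 39 per group, which does not fit.

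**2. Gain from baseline adjustment, with SD 22 as the SD of the 12-week score.** Residual SD = 22 × √(1 − r²); SE = residual SD × √(2/49.4); half-width of the 95% CI = 1.985 × SE; power from the two-sample t distribution.

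| r | Variance removed (r²) | Residual SD | SE | Half-width | Power at 15 points |
|---|---|---|---|---|---|
| unadjusted | 0 | 22.0 | 4.43 | 8.8 | 92% |
| 0.4 | 16% | 20.2 | 4.06 | 8.1 | 96% |
| 0.5 | 25% | 19.1 | 3.83 | 7.6 | 97% |
| 0.7 | 49% | 15.7 | 3.16 | 6.3 | over 99% |

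**3. The same, with SD 22 as the SD of change.** The sample size paragraph speaks of improvement, so this reading is open. With equal SDs at both times, SD of change = SD of score × √(2(1 − r)), so SD of score = 22/√(2(1 − r)).

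| r | SD of score | Unadjusted power | ANCOVA power |
|---|---|---|---|
| 0.4 | 20.1 | 96% | 98% |
| 0.5 | 22.0 | 92% | 97% |
| 0.7 | 28.4 | 74% | 95% |

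**4. Chance imbalance.** If the baseline SD is also 22, the SE of the baseline difference is 22 × √(2/52) = 4.3 points. Its 95% range is ±1.96 × 4.31 = ±8.5 points, and a gap above 5 points either way has probability of about 25%. With equal SDs, a gap shifts the expected unadjusted result by r times the gap. A 5-point gap shifts it by 2.0, 2.5 or 3.5 points, and an 8.5-point gap by 3.4, 4.2 or 5.9 points (r = 0.4, 0.5, 0.7).

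Conditional on a gap k standard errors wide, type I error is 1 − Φ((1.96 − rk)/√(1 − r²)) + Φ((−1.96 − rk)/√(1 − r²)). At k = 1.96 this is about 13% for r = 0.5 and 20.5% for r = 0.7. Averaged over all randomisations it is 5%.

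**5. The switch of test.** Simulation of 6,000 trials with 49 per arm, using a Shapiro-Wilk check at 0.05 in each arm (an assumed criterion):

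- Normal data: type I error 5.1%, power 92%.
- Skewed (gamma) data: type I error 4.3%, power 96%.

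**The case against.** The strongest case on the other side is that the planned analysis is valid and adequately powered. Under the plain reading of SD 22 it has about 92% power at the planned 15 points, above the 90% target. Its standard error already allows for chance imbalance, so it is unbiased with 5% type I error over randomisations. The regression sentence refers to baseline scores, its list is only illustrative, and an article may leave the full covariate list to a longer document. The rule for switching tests is written down in advance.

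Most of this stands, and it rules out four stronger readings that a reader might infer:

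- **That the plan ignores baseline DASH, or makes the regression secondary.** The text neither excludes baseline DASH from the regression nor ranks the two analyses.
- **That the trial is underpowered or its test invalid.** Power falls below target only if SD 22 is a change SD and r is high.
- **That a baseline gap passes in full into the result.** It passes at r times its size.
- **That the switch inflates type I error or wastes precision.** The simulation shows neither, and the precision loss comes from leaving out baseline.

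The objection does not dispose of the core. The article does fix a named test for the primary outcome, and that test has no baseline term. This is a stated choice and not an omitted detail. Writing the switching rule in advance also does not make a rank comparison answer a question posed in DASH points.

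**Conclusion.** The point holds as one of efficiency, robustness and clarity. It is a change that should be made, not a flaw that invalidates the trial. The named primary test gives up between 16% and 49% of residual variance for r from 0.4 to 0.7, which is 0.7 to 2.5 points on the half-width of the confidence interval. It also leaves the realised result open to a chance baseline gap. The documents do not settle which analysis is decisive or whether baseline DASH is in the regression.

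The size rests on r, which the article does not give, and on which SD the 22 represents. If it is the SD of the 12-week score, power at 15 points is adequate with or without adjustment. If it is the SD of change and r is 0.7, adjustment separates 74% from 95%. The imbalance figures further assume a baseline SD of 22. The harm from the test switch is confined to an effect measure that depends on the data.

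**What to change.** In the Statistical analysis section, name one primary analysis: ANCOVA of the 12-week (T2) DASH score on arm, with baseline DASH as covariate and the already named age, gender and duration of complaints alongside it. Report the adjusted mean difference in DASH points with its 95% CI, whatever a normality check shows. Keep the Mann-Whitney test as a sensitivity analysis only. In the Sample size section, state whether SD 22 refers to the 12-week score or to the change.

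The cost is two or three sentences. No new data, visits or patients are needed, because baseline DASH is already collected and a regression is already planned.

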## Discussion

Since there is little evidence for the efficacy of physical therapy interventions in some shoulder disorders, there is a need for further research. Therefore we will perform a randomised clinical trial dealing with the effect of physical therapy interventions aimed to inactivate MTrPs on pain and impairment in shoulder function in a population of chronic a-traumatic shoulder patients. To the best of our knowledge, few studies of the efficacy of MTrP therapy are published. We choose for an intervention strategy that best reflects daily practice. We excluded manual high velocity thrust techniques and intramuscular MTrP release by dry needling, because these interventions are not commonly used by Dutch physical therapists and not all participating therapists were skilled to perform these techniques at the beginning of the study. In most physical therapy interventions, blinding of the patient and the therapist is not possible. The observers will be blinded for the allocation procedure. The results of this trial will be presented as soon as they are available.
